### Data management and statistics

The study is conducted in compliance with the EU’s General Data Protection Regulation (GDPR) [59]. Participant’s data will be processed pseudonymized. All data will be first documented in paper-pencil form and then entered in an electronic data base for further analyses. Programed plausibility checks (including, i.e., valid value checks and range checks) will be performed after assessment completion. All data are to be evaluated descriptively (i.e., mean, standard deviation, median, ranges, frequencies) to evaluate prevalence of MetS and of the respective risk factors (in the full study cohort and in defined subgroups, e.g., according to age and recruitment regions). The data sets will be evaluated conducting full case and complete case analyses. Paired *t* tests and Pearson’s Chi-squared tests are planned to evaluate any gender differences to all predictor and outcome variables. To evaluate the association of MetS with other assessed factors and variables (e.g., anthropometric parameters, age, sex, urbanity, physical activity, stress perception, social support, identified abnormalities, or diseases), inferential statistics (e.g., regression analysis, ANOVA), and cluster analyses are planned.

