### Recruitment strategy

In part A, a passive recruitment strategy will be applied with a target population of all residents of Brandenburg that voluntarily approaches to the mobile diagnostic units [31]. Participants will be recruited at different locations in Brandenburg by setting up the mobile diagnostic unit in mainly rural areas far from metropolitan regions. In order to reach as many people as possible, targeted public relations work will be carried out and the mobile study unit is to be placed at market places and at events such as health days and festivals. Cooperation with companies and public administrations is planned in order to make the study known to their employees and encourage them to participate. Announcements will be done by advertising posters, articles in local newspapers and internal newsletters in companies, reports at local radio stations, and at online event calendars of communities and towns. On site, interested passers-by and participants will be directly addressed and recruited spontaneously.

For part B, potentially eligible participants who were diagnosed with MetS in part A and give consent to be re-contacted, will be recruited by telephone. Eligible persons will be allocated to the mobile examination or telephone interview in study part B.

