### Sample size determination

For the pilot study (test-retest, reliability), 50 participants will be recruited. For part A and part B, sample size determination was based on the results of Moebus et al. (2008), a nationwide study on primary care patients that revealed an age-standardized MetS prevalence of 22% in Brandenburg [19]. The aim is to recruit 5000 participants in part A to develop the “Mobile Brandenburg Cohort,” and to identify approximately 1100 participants with MetS who are potentially eligible for later recruitment for part B.

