### Study status

Participants must be recruited and enrolled for each of the three study parts. Recruitment for the pilot study has been completed with 50 participants. Planned recruitment and measurement days for main study part A in 2020 had to be canceled due to the COVID-19 pandemic. Therefore, recruitment for study part A has ended for the time being with a total of 3.931 participants enrolled. Recruitment for study part B is ongoing and not yet completed. For the mobile examination, 93 participants have been enrolled by beginning of 2020. Due to the COVID-19 pandemic, the focus is on recruitment for the telephone interviews of study part B, for which 94 participants have been enrolled so far.

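### The planned analyses of part B deal with missing items among those who take part, not with selection from part A into the part B examination, although part A data could be used to address it

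*Protocol article*

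**What the plan says.** Under Outcomes, the protocol article gives part B two main results: medical validation of the MetS screening, and the prevalence of secondary diseases not diagnosed before. Data management and statistics says that all data are summarised descriptively, with frequencies among the listed summaries, and continues: "The data sets will be evaluated conducting full case and complete case analyses". It names no method specific to part B prevalence.

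Entry to part B has several steps. Participants requires MetS in part A, no known secondary disease, and separate written consent for each part. Recruitment strategy adds that "potentially eligible participants who were diagnosed with MetS in part A and give consent to be re-contacted, will be recruited by telephone", after which eligible people go either to the mobile examination or to a telephone interview.

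Sample size determination takes as its basis a study that "revealed an age-standardized MetS prevalence of 22% in Brandenburg", and aims "to identify approximately 1100 participants with MetS who are potentially eligible for later recruitment for part B". Study status reports that part A stopped for the time being "with a total of 3.931 participants enrolled". On part B it says: "For the mobile examination, 93 participants have been enrolled by beginning of 2020". For the telephone interviews it gives a count "for which 94 participants have been enrolled so far", and it notes: "Recruitment for study part B is ongoing and not yet completed".

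**The concern.** Analyses of all and of complete cases differ in how they treat missing items among people already in the data set. They do not differ in who is in it. If the two agree for part B, that says nothing about selection between the part A diagnosis and the examination, yet a reader could take the agreement as reassurance.

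Selection is plausible. A person must agree to re-contact, be reached, consent again and be placed on the mobile route, which takes about an hour and includes an exercise ECG on a bicycle ergometer. Attendance unrelated to health would be a strong assumption. The raw proportion may then describe those who came rather than eligible people with MetS.

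Part A already collects useful information on those not examined: MetS components, HbA1c, weight and height, medication, a list of known diseases, sociodemographics, stress, life events and physical activity (Table 2). The stated analysis makes no use of it for this outcome.

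**Working it through.** **Inputs from the article.** Part A target 5,000 and prevalence 22% (Sample size determination); 3,931 enrolled in part A, 93 examined, 94 interviewed by telephone (Study status).

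**1. The plan's own figure.** 5,000 × 0.22 = 1,100. This reproduces the stated number of MetS cases.

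**2. Expected cases at actual enrolment.** 3,931 × 0.22 = 865.

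**3. Interim share reached.**
- Examined: 93/865 = 10.8%.
- Examined or interviewed: (93 + 94)/865 = 187/865 = 21.6%.

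**4. Sensitivity to MetS prevalence (30% and 40% are assumptions).**
- 30%: 3,931 × 0.30 = 1,179; 93/1,179 = 7.9%.
- 40%: 3,931 × 0.40 = 1,572; 93/1,572 = 5.9%.

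**5. Sensitivity to eligibility.** The number free of known secondary disease is not reported. With 865 MetS cases and an assumed eligible share e, the examined share is 93/(865 × e):
- e = 80%: 93/692 = 13%.
- e = 60%: 93/519 = 18%.
- e = 40%: 93/346 = 27%.
- e = 30%: 93/259 = 36%.

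The examined would be at least half of the eligible only if 2 × 93 = 186 or fewer were eligible (186/865 = 21.5%). As Participants and Recruitment strategy are written, both routes need part B eligibility, so the 187 already enrolled are themselves eligible, and 93/187 = 49.7%. On the reported counts, then, about half or more of the eligible had not been examined. That last check needs no prevalence assumption.

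**6. What selection on a measured variable could do (all figures assumed).** Take two equal part A risk strata with true prevalence 30% and 10%, so 20% overall. If the high-risk stratum attends r times as often, the raw prevalence is (0.30r + 0.10)/(r + 1):
- r = 0.5: 0.25/1.5 = 16.7%.
- r = 2: 0.70/3 = 23.3%.
- r = 3: 1.00/4 = 25.0%.

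Weighting by inverse attendance within stratum restores 20% each time, provided attendance depends only on the stratum.

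**7. Selection on the undiagnosed disease itself (also assumed).** With true prevalence 20% and attendance ratio r between affected and unaffected people, raw prevalence is 0.2r/(0.2r + 0.8): 11.1% at r = 0.5, 27.3% at r = 1.5, 33.3% at r = 2. Part A weighting cannot fully remove this.

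**8. Sampling error for scale.** With 93 examined and 20% prevalence, the 95% half-width is 1.96 × √(0.2 × 0.8/93) = 8.1 percentage points. The distortions in step 6 (3 to 5 points) lie within it; the largest in step 7 (13 points) exceeds it.

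**The case against.** The sentence that speaks of prevalence in the analysis section names MetS and its risk factors, not secondary diseases. That part B will report a raw proportion is therefore inferred from the statement that all data are treated descriptively. A condensed article may also leave non-response weighting to a fuller document. Both remarks are fair, and the absence of weighting alone would not be a finding. What stands is that the article does state its analysis approach for all data, and that approach cannot bear on selection into part B.

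A reader might infer from the counts that nine in ten MetS cases drop out. The documents do not support this. Part B is a separately consented second stage, people with known secondary disease are excluded by design, and the telephone interview is one of its two routes. Recruitment was open and had been turned towards the telephone by the pandemic. The number invited is not given, so refusal cannot be told apart from not yet having been asked.

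Nor is 10.8% an upper bound in general. A higher MetS prevalence lowers it, but excluding ineligible people and continuing recruitment both raise it.

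The telephone route answers the concern only in part. It covers comorbidity, depression and cognition, but has no clinical examination, ECG or blood test, and uses different instruments for depression and cognition (Table 2).

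Finally, the observed yield among those examined is the right figure for judging the usefulness of the mobile unit, which Outcomes also intends. That is a good reason to keep the raw figure.

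**Conclusion.** The concern holds in a limited form. The stated analyses address missing items among participants and leave selection from part A into the part B examination untouched, for an outcome that the article calls main. The participation figure, 93 of about 865 or 10.8%, is an interim illustration that rests on the 22% prevalence and on a denominator that includes ineligible people; the share among eligible people is unknown.

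The size of any bias cannot be derived, because the article gives no part B results and no attendance by subgroup. A reader might take the 11% to 33% range in step 7 as the error that weighting would correct. It is not: it assumes attendance driven by the undiagnosed disease itself. The part that part A data can correct is closer to step 6, where a twofold attendance ratio between measured strata moves 20% to 23.3%. For this reason, and because about 93 examined people support only a small model, the adjusted estimate belongs beside the raw one and should not replace it.

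**What to change.** Add three items to the part B analysis:

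1. Report the number of part A MetS cases without known secondary disease, as recorded in part A, as the denominator. It will be approximate: Medical history shows that part A asks about a short list of diagnoses, while Background also links MetS to conditions not on it, such as depression, dementia and fatty liver disease.
2. Tabulate examined, telephone-interviewed and non-participating eligible people side by side on part A data. A further split into not reached and declined would need contact records, which the article does not mention.
3. Beside the raw prevalence, report an estimate weighted or standardised to those eligible cases, using a small prespecified set of part A variables, for example age, sex, number of MetS components and HbA1c.

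The first two items and the estimate need no further contact with participants. The costs are analysis time and wider intervals, possibly noticeably so with about 93 examined. The report should state three limits: only selection on measured part A variables is corrected; people who could not be examined by design are not represented by weighting; and the target is itself a walk-in sample, so the adjusted figure describes eligible part A participants and not the population of Brandenburg.

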## Methods/design

### Study design and flow

After development and validation of mobile laboratory and diagnostic units for a van and a truck (pilot study), a prospective cohort study is to be implemented: main study “part A” is a cross-sectional study, in which baseline measurements will be performed, and MetS prevalence and associated factors are to be evaluated by screening participants in a mobile diagnostic unit near to the participant’s homes. In “part B,” persons previously diagnosed with MetS in part A will be examined (mobile medical examination in a truck or phone-based interviews) to assess secondary diseases of MetS (Fig. 1). The feasibility of the mobile diagnostic approach (part A and B) is to be evaluated. All parts of the study will form the basis for the establishment of the “Mobile Brandenburg Cohort,” which will allow further longitudinal studies.

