### Participants

To be eligible for part A, adults (men and women) with an age between 40 and 70 years will be recruited. As the study aims to implement prevention strategies to reduce morbidity and mortality of the population due to MetS, the target population for inclusion are persons with emerging risk for MetS, but less probable presence of (multiple) manifested secondary diseases. Therefore, the age range was chosen to reach participants within the working and retirement age that feature a number of age-related risks for the presence of MetS and for development of its secondary diseases [29, 30]. To be eligible for part B, participants have to be diagnosed with MetS in part A, but have to have no (known and diagnosed) secondary disease. To be eligible for all study parts, participants have to be able to understand the study information and must provide written informed consent for each part.

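### Gender differences in continuous variables are assigned to paired t tests, but men and women are independent, unmatched participants, so the named test is undefined for these comparisons

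*Protocol article*

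**What the plan says.** The protocol article, under Data management and statistics, plans: "Paired *t* tests and Pearson’s Chi-squared tests are planned to evaluate any gender differences to all predictor and outcome variables". Of the tests named in that section, these are the only two tied to one specific contrast.

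The rest of the article shows who is being compared:

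- Participants: "adults (men and women) with an age between 40 and 70 years will be recruited".
- Recruitment strategy: "a passive recruitment strategy will be applied with a target population of all residents of Brandenburg that voluntarily approaches to the mobile diagnostic units", and at the sites "interested passers-by and participants will be directly addressed and recruited spontaneously".
- Study design and flow: "main study “part A” is a cross-sectional study, in which baseline measurements will be performed".

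The next sentence of the statistics section lists sex among the factors whose association with MetS will be studied by regression, ANOVA or similar methods.

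**The concern.** A paired t test is a one-sample test on within-pair differences. It has a meaning only if each man's value belongs with one particular woman's value. The design creates no such link. People enter one at a time, the numbers of men and women are not fixed, and part A is cross-sectional.

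The sentence is also at odds with itself. It names Pearson's chi-squared test for the same contrast, and that test treats the two sexes as independent groups.

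The sentence covers all predictor and outcome variables. At stake are therefore the gender comparisons of blood pressure, lipids, glucose, waist circumference, HbA1c and the questionnaire scores. An analyst who follows the text either cannot run the test or has to invent a pairing.

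**Working it through.** **The plan's own figure.** The sample size section expects to "identify approximately 1100 participants with MetS who are potentially eligible for later recruitment for part B" out of 5,000, from a prevalence of 22%: 5,000 × 0.22 = 1,100. This reproduces. It does not depend on the gender test.

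**Is there a source of pairs?** The sections on participants, recruitment, design and procedures describe no matching by sex, no recruitment of couples and no sex quota. Paired data do exist elsewhere: the pilot compares point-of-care analyzers with a reference laboratory and examines test-retest reliability. The sentence at issue, however, applies the paired test to gender.

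**Can the test be run as written?** With 2,162 and 1,769 values (a 55/45 split of 3,931), a standard paired t test routine stops with an error because the two lists differ in length.

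**What if pairs were forced?** Inputs: N = 3,931 enrolled in part A (Study status). The article gives no sex split, so the share f of the larger sex is an assumption, varied from 50% to 70%. A true difference of 0.1 SD and a two-sided alpha of 0.05 are also assumptions.

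- Larger group n₁ = f × N; smaller group n₂ = N − n₁; people dropped = n₁ − n₂.
- Standard error in SD units, independent test: √(1/n₁ + 1/n₂).
- Standard error in SD units, n₂ random pairs of unrelated people: √(2/n₂).
- The ratio of the second to the first simplifies to √(2n₁/N) = √(2f).
- Power ≈ Φ(0.1/SE − 1.96).

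| f | n₁ / n₂ | Dropped | SE ratio | Power, independent | Power, forced pairs |
|---|---|---|---|---|---|
| 50% | 1,966 / 1,965 | 1 | 1.00 | 0.880 | 0.880 |
| 55% | 2,162 / 1,769 | 393 (10%) | 1.05 | 0.877 | 0.845 |
| 60% | 2,359 / 1,572 | 787 (20%) | 1.10 | 0.867 | 0.801 |
| 65% | 2,555 / 1,376 | 1,179 (30%) | 1.14 | 0.849 | 0.746 |
| 70% | 2,752 / 1,179 | 1,573 (40%) | 1.18 | 0.819 | 0.680 |

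Worked at 60%: the independent SE is √(1/2,359 + 1/1,572) = 0.0326, so power is Φ(3.07 − 1.96) = 0.867. The forced-pairs SE is √(2/1,572) = 0.0357, so power is Φ(2.80 − 1.96) = 0.80.

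**Type I error.** In 4,000 simulated data sets with no true difference at the 60/40 split, rejection rates at 0.05 were 0.048 for Welch and 0.049 for arbitrary pairing. Random pairing therefore wastes data but does not bias the test. Pairing people by their ordered outcome values, an extreme case that nobody proposes, rejected about 95% of the time. The result thus depends on how pairs are made, and the article gives no rule for making them.

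**The case against.** The case for treating this as minor is strong in several respects.

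- **Gender contrasts are secondary.** They are neither a stated aim nor a central outcome. Prevalence is to be evaluated descriptively, and no sample size figure or feasibility criterion uses a gender test. This stands.
- **Sex and MetS have another route.** MetS status by gender goes to the chi-squared test, which suits independent groups, and the next sentence of the plan puts sex into regression or ANOVA. This stands, and it leaves only the continuous contrasts exposed.
- **It may be a slip for unpaired.** That is plausible, and software will usually expose it, since the test fails on unequal groups. It lowers the risk of a wrong published result but does not remove the error. The text names a paired test, and a separate analysis plan would have to contradict the protocol to put it right.

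A reader might infer that the planned gender p-values are biased, will swing with the order of the records, or will rest on a fixed fraction of the cohort. The documents do not support this. Nothing in them plans an arbitrary pairing or the discarding of participants, random pairing keeps the error rate near nominal, and no sex split is given. The table in the working shows what forced pairing would cost; it does not predict what the sponsor will do.

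**Conclusion.** The point holds as an error in a named method. The paired t test is undefined for comparing unmatched men and women, and this affects every continuous gender comparison. The error follows from the text and needs no assumption.

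Its size under forced pairing does rest on assumptions. Between 1 and 1,573 of 3,931 people would be lost for a 50% to 70% share in the larger sex. For a difference of 0.1 SD, power would be unchanged at an even split and would fall from 0.819 to 0.680 at 70/30.

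It would go too far to say that the study's main results are at risk. The part A prevalence outcome and the regression, ANOVA and cluster analyses of MetS do not use this test. The correction should be made, at a severity below must-fix.

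**What to change.** In the gender sentence under Data management and statistics, replace the paired t tests with independent-samples t tests; the Welch form is a sensible default because group sizes and variances may differ. Keep Pearson's chi-squared test for categorical variables. If a separate analysis plan exists, check that it says the same.

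The cost is one phrase. No data, sample size or design element changes, and all enrolled participants with a value for the variable contribute.

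### Gender differences are to be tested without adjustment in a walk-in sample aged 40 to 70, so any difference in age mix between attending men and women can appear as, or mask, a gender difference, chiefly in the part A variables other than MetS

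*Protocol article*

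**What the plan says.** All citations are to the protocol article.

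- **Gender comparisons** (Data management and statistics). "Paired *t* tests and Pearson’s Chi-squared tests are planned" for this purpose, and the scope is every variable: "Chi-squared tests are planned to evaluate any gender differences to all predictor and outcome variables". No covariate, stratification or standardisation is attached.
- **Associations with MetS** (next sentence of the same section). The aim is "To evaluate the association of MetS with other assessed factors and variables (e.g., anthropometric parameters, age, sex, urbanity" and further examples, and the methods are "inferential statistics (e.g., regression analysis, ANOVA), and cluster analyses are planned". The outcome of these models is MetS. Age and sex are listed as factors, but the sentence does not say that they enter one model together.
- **Description by age** (same section). Prevalence of MetS and of its risk factors is to be described "in the full study cohort and in defined subgroups, e.g., according to age and recruitment regions".
- **Sampling** (Recruitment strategy). The target is "all residents of Brandenburg that voluntarily approaches to the mobile diagnostic units". Among the channels, "Cooperation with companies and public administrations is planned in order to make the study known to their employees". Market places, health days and festivals are others. No age or sex quota is given.
- **Age** (Participants). Eligibility runs from 40 to 70 years. The range was chosen to reach people who "feature a number of age-related risks for the presence of MetS".

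**The concern.** A t test and a Pearson chi-squared test compare two groups as they stand. By the protocol's own account, age is related to MetS risk, and recruitment does nothing to give the men and women who attend the same age distribution. A workplace visit and a weekday market may well draw different ages of each sex. Any such difference passes straight into the crude contrast for every variable that changes with age.

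Part A had 3,931 participants when the article was written, so the standard errors are small and a modest age gap can move a p-value. The distortion can go either way: it can create a difference where none exists within age, or cancel one that does. For variables other than MetS, these crude tests are the only method that the section explicitly assigns to gender differences.

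**Working it through.** **The plan's own figure.** Sample size determination expects about 1,100 participants with MetS from 5,000 at 22%. 5,000 × 0.22 = 1,100, which reproduces. The article gives no sex ratio, age distribution, age-specific prevalence, alpha or power for a gender comparison. There is therefore no stated gender figure to reproduce, and what follows is an illustration.

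**Inputs from the article:** n = 3,931 (Study status) and overall MetS prevalence of 22% (Sample size determination).

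**Assumed inputs:** a 50:50 sex split; one third of the sample in each of the age bands 40–49, 50–59 and 60–70; MetS prevalence of 14/22/30% in these bands, with 18/22/26% as a flatter and 10/22/34% as a steeper gradient; no gender effect within any band; two-sided 5% level. An imbalance of s means that the men's share in the oldest band exceeds the women's by s, and their share in the youngest band falls short by s.

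**Binary variable**

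- Spurious difference: d = s × (p_old − p_young). For s = 0.10 and 14/22/30%: 0.10 × (0.30 − 0.14) = 0.016, that is 22.8% against 21.2%.
- Standard error: SE ≈ √(0.22 × 0.78 × 4/3,931) = 0.0132.
- z = 0.016/0.0132 = 1.21. Rejection probability = Φ(1.21 − 1.96) + Φ(−1.21 − 1.96) = 0.23.

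| Prevalence by band | s | Spurious difference (points) | Rejection |
|---|---|---|---|
| any | 0 | 0 | 5% |
| 14/22/30% | 5 points | 0.8 | 9% |
| 14/22/30% | 10 points | 1.6 | 23% |
| 14/22/30% | 20 points | 3.2 | 68% |
| 18/22/26% | 10 points | 0.8 | 9% |
| 10/22/34% | 10 points | 2.4 | 44% |

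**Masking.** Use the same SE and the 14/22/30% gradient. Suppose men are truly 3.2 points higher within age. With equal age mix the test rejects 68% of the time. If the women are older by s = 10 points, the crude difference falls to 3.2 − 1.6 = 1.6 points and rejection to 23%.

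**Continuous variable.** Assume a slope of 5 mmHg per decade, SD 17 mmHg and a mean age gap of 2 years. The bias is 5 × 0.2 = 1.0 mmHg. SE = 17 × √(4/3,931) = 0.54, z = 1.84, rejection 45%.

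**Does adjustment repair it?** A separate model used N = 5,000, half women, and two age bands with prevalence 12% and 32%. It was simulated 1,000 times per setting with no gender effect within age.

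| Shift in age mix (points) | Crude chi-squared rejects | Sex term with age in a logistic model rejects |
|---|---|---|
| 0 | 5% | 6% |
| 5 | 14% | 6% |
| 10 | 38% | 5% |
| 15 | 72% | 4% |

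Over a wider grid of that two-band model (shifts of 2 to 15 points, prevalence gaps between bands of 10 to 30 points, N of 3,931 or 5,000, 50% or 60% women), the spurious difference ran from 0.2 to 4.5 points and crude rejection from 5% to 97%. The mechanism is certain. Its size is set by inputs that the article does not supply.

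**The case against.** The strongest reply is that nothing here is invalid. A crude comparison asks whether the men and women in this sample differ, and for that question the test keeps its level. It misleads only if read as a difference at equal age, and the article never says it will be read that way. Age is presumably among the variables to be compared by gender, so an imbalance would be visible. Gender contrasts are not among the five aims or the outcomes. The article condenses a fuller plan, and covariate sets are commonly left there. All of this stands, and it limits how serious the point is. It does not remove it: the article names specific unadjusted tests for all variables and does not label them descriptive. Seeing an age imbalance is also not the same as allowing for it.

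Three stronger readings are tempting, and the article does not support them.

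- *False gender differences will be reported.* The article does not say, or imply, that attending men and women differ in age. The harm is conditional on that.
- *The gender contrast for MetS is left unadjusted.* The next sentence plans regression for MetS with age and sex among the example factors. Joint adjustment is the ordinary content of such a model, although it is not spelled out. The MetS prevalences above illustrate the mechanism for a binary variable; they do not show that MetS is uncovered.
- *The same harm applies in part B.* Study status gives 93 mobile and 94 telephone participants so far. With the continuous example at n = 93, SE = 17 × √(4/93) = 3.5 and the 1.0 mmHg bias gives about 6% rejection, close to nominal. The bias would be the same, but significance would hardly change.

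**Conclusion.** The point holds as a conditional weakness in a named method. The planned gender tests take no account of age in a self-selected sample spanning 30 years of age, and the gap is mainly in the part A variables other than MetS. How much it matters cannot be read from the article: nothing is lost if the age mix is equal, and the rejection rates tabulated above rest entirely on assumed age gradients and an assumed imbalance. It threatens neither the prevalence estimate nor the stated aims. It is worth correcting because the correction is almost free.

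The same sentence has a plain error of its own. Men and women are independent, unmatched groups, so a paired t test does not apply. Changing that word alone would leave the age question untouched.

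**What to change.** Rewrite the sentence on gender in Data management and statistics along these lines:

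- Report crude means and percentages by gender, labelled as description.
- Base inference about gender differences on one regression per variable with sex and age as terms: linear for continuous variables, logistic or risk-difference for binary ones. Report the age-adjusted difference (or odds ratio, if logistic) with its 95% CI.
- For MetS, state that age and sex enter the planned regression together.
- Where a crude t test is kept, specify an independent-samples test, for example Welch's, and delete the word for pairing.

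The cost is a sentence or two of text and one model per variable. Age is an eligibility criterion and so should be known for everyone; no new data are needed.
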